## Abstract

**Background::**

Atopic dermatitis (AD) is a common eczematous skin disorder that profoundly reduces the quality of life due to intractable pruritus. Excellent therapeutic success of the anti-interleukin 4 receptor-α antibody dupilumab in clinical trials and a real-world clinical context indicates the crucial roles of interleukin (IL)-4 and IL-13 in the pathogenesis of AD. Along with the clinical improvement in skin scores and pruritus, dupilumab significantly and progressively reduces and normalizes the upregulated expression of T helper type 2 signatures such as Chemokine (C-C motif) ligand (CCL)17, CCL18, CCL22, and CCL26 in the lesional skin of AD. However, no blood/serum biomarkers are known to predict good or poor outcome in patients with AD treated with dupilumab.

**Methods::**

Patients are at least 18 years of age and have moderate-to-severe AD with Eczema Area and Severity Index (EASI) ≥16, Investigator's Global Assessment ≥3, and body surface area ≥10%. We are going to enroll more than 130 subjects from 18 medical facilities. Clinical objective findings will be evaluated by EASI. Subjective symptoms will be assessed by Patient-Oriented Eczema Measure, Numerical Rating Scale for Pruritus (Pruritus-NRS), Skin Comfort-NRS, and Treatment Satisfaction-NRS. We will measure 18 blood/serum biomarkers including % eosinophils in blood cell count, lactate dehydrogenase, total IgE, soluble interleukin 2 receptor, CCL17, CCL18, CCL22, CCL26, CCL27, IL-13, IL-22, IL-24, IL-25, IL-31, IL-33, thymic stromal lymphopoietin, periostin, and squamous cell carcinoma antigen-2. The clinical evaluation and biomarker sampling will be performed at 0, 2, 4, 8, and 16 weeks of dupilumab treatment. We will also perform proteomic analysis (of roughly 300 proteins) of the patients’ sera obtained at 0 and 2 weeks of treatment. The primary endpoint is the association between “baseline levels of 18 biomarkers” and “% change from baseline of EASI at 16 weeks of dupilumab treatment.”

**Discussion::**

This is the first clinical trial to explore the biomarkers, including potential proteomic markers, most strongly associated with improvement in EASI in patients with moderate-to-severe AD treated with dupilumab for 16 weeks (B-PAD study). A limitation is that we will only enroll Japanese patients.

## Introduction

1

Atopic dermatitis (AD) is a common eczematous skin disorder, the incidence in the first 5 years of childhood of which is 10% to 16.5%. It is generally considered to have increased in prevalence worldwide, at least from the 1980 s to the early 2000 s.^[1]^ Clinical features of AD include skin inflammation, barrier dysfunction, and chronic pruritus.^[2]^ Its course involves chronic relapse with intense pruritus, which reduces the quality of life and decreases treatment satisfaction among afflicted patients.^[3–5]^ Excellent therapeutic success of the anti-interleukin 4 receptor-α antibody dupilumab in clinical trials and in a real-world clinical context has indicated the crucial roles of T helper type 2 (Th2) cytokines, interleukin (IL)-4 and IL-13, in the pathogenesis of AD.^[6–8]^ Along with the clinical improvement in skin scores and pruritus, dupilumab significantly and progressively reduces and normalizes the elevated expression of Th2 signatures such as Chemokine (C-C motif) ligand (CCL)17, CCL18, CCL22, and CCL26 in the lesional skin of AD.^[9,10]^ Other lesional and blood markers including eosinophils,^[11–13]^ lactate dehydrogenase (LDH),^[14]^ total immunoglobulin E (IgE),^[15]^ soluble IL-2 receptor,^[16]^ CCL27,^[14]^ IL-13,^[17]^ IL-22,^[9]^ IL-24,^[18,19]^ IL-25,^[20]^ IL-31,^[21,22]^ IL-33,^[23]^ thymic stromal lymphopoietin (TSLP),^[24]^ periostin,^[9,25]^ and squamous cell carcinoma antigen-2 (SCCA2)^[26,27]^ are elevated in AD and show substantial correlations with its disease activity.

It is now recognized that AD is not a single or monophenotypic disease, but is composed of heterogenous groups.^[11,28–30]^ In general, we have classified AD patients based on clinical features such as age (pediatric, young adult vs. elderly),^[30,31]^ clinical course (acute vs. chronic),^[32]^ IgE dependence (atopic vs. non-atopic),^[33,34]^ and ethnicity (Caucasian vs. non-Caucasian).^[35]^ In addition, recent approaches based on the molecular mechanisms have subdivided AD into different endoypes, for example, Th2 vs. Th2 + Th17,^[36–38]^ and clinical severity + Th2 / interferon-α/β.^[39]^ The phenotypic and endotypic differences in AD have led to a basis for stratifying patients. Stratifying patients by endotype may be particularly meaningful for the application of molecularly targeted drugs such as dupilumab. Although biomarkers representing the Th2 signature tend to decrease upon dupilumab treatment, the individual degrees of response of biomarkers as well as the rates of clinical improvement vary.^[40,41]^ In addition, it is not fully understood what kinds of biomarkers are responsible for a good/poor clinical outcome of dupilumab treatment.

The purpose of this study is to explore the biomarkers, including potential proteomic markers, that are most strongly associated with clinical improvement in patients with moderate-to-severe AD treated with dupilumab.

## Methods/Design (Protocol version 1.0, registered on July 8th, 2019)

2

### Study hypothesis/benefit

2.1

Certain biomarkers, including proteomic ones, may be associated with a good/poor clinical response to dupilumab. This information could be very useful for patients for whom the initiation of dupilumab therapy is being considered, given its high cost. Using meaningful stratification of patients, we can expect to increase efficacy of drugs and decrease the economic burden on patients. In addition, new Th2-related serum proteins may be highlighted by proteomic analysis as future target molecules in AD.

### Study design

2.2

This is a multi-center, prospective, observational study in which samples/information will be obtained in Japan. This exploratory study will basically be carried out under real-world standard treatment guidelines. We are going to enroll more than 130 subjects from 19 medical facilities joining a consortium. The patients are to cease oral immunosuppressive drugs, oral steroids, or phototherapy at least 1 week before the start of injections of dupilumab. None of the patients is to have any previous experience of dupilumab treatment. They are to be at least 18 years of age, have moderate-to-severe AD with Eczema Area and Severity Index (EASI) ≥16, Investigator's Global Assessment (IGA) ≥3, and body surface area ≥10%, and be individuals for whom topical treatment of steroids provided inadequate control or was medically inadvisable, and had chronic AD for at least 3 years before the start of this study. The use of systemic steroids, systemic calcineurin inhibitors, and phototherapy is not allowed after the initiation of dupilumab.

The continued use of topical steroids, topical calcineurin inhibitors, topical moisturizers, and oral antihistamines used at baseline is allowed. Change of topical drugs to more potent ones is not allowed. The use of ocular, intranasal, or inhalant steroids and calcineurin inhibitors is allowed throughout the study, as is the use of anti-histamine drugs. Subjects are to receive subcutaneous injections of dupilumab (initial dose 600 mg, then 300 mg) biweekly for 16 weeks.

All investigators involved in this study shall carry out this study in accordance with the latest editions of the Declaration of Helsinki and “Ethical Guidelines for Medical and Health Research involving Human Subjects” of the Ministry of Health, Labour and Welfare, Japan. The study protocol has been approved by the Clinical Research Network Fukuoka Certified Review Board (CRB7180004). This study has been registered with the University Hospital Medical Information Network Clinical Trials Registry (UMIN000037307). The enrollment period is set to run from October 10, 2019. Last follow-ep date will be set on September 30, 2021.

### Sample size estimates

2.3

The target number of 130 patients aimed to be enrolled was determined based on past experiences and feasibility. From previous phase 3 trials,^[7]^ since it is assumed that approximately 25% of enrolled patients with dupilumab treatment will discontinue the treatment, a plan was set to enroll more than 130 subjects and perform data analysis of at least 100 subjects.

### Eligibility criteria

2.4

Inclusion criteria are as follows:

(1)chronic AD that has been present for ≥3 years at enrollment;(2)moderate-to-severe patients with EASI score of ≥16, IGA score of ≥3, and body surface area ≥10% at enrollment (excluded if inflammation is limited to the head and neck region);(3)no treatment history of dupilumab;(4)patients in whom topical steroid treatment provides insufficient inhibition or is medically inadvisable;(5)patients aged ≥18 years and ≤70 years at enrollment; and(6)patients who are able to completely understand the study plan and to provide signed informed consent.

Exclusion criteria are as follows:

(1)patients treated with oral immunosuppressive drugs, oral steroid, or phototherapy within 4 weeks before dupilumab administration;(2)female patients who are breastfeeding, pregnant, or have the possibility of being pregnant; and(3)any other patients who are regarded as unsuitable for this study by the investigators.

Patient enrollment is performed by a central enrollment method. The investigators confirm that the study subjects meet all of the inclusion criteria and do not meet any of the exclusion criteria, and enter all of the necessary information for patient enrollment in the electronic data capture (EDC) system (Viedoc 4). Data monitoring including adverse events are periodically and independently performed by Clinical Research Support Center Kyushu (CReS Kyushu). Protocol kick-off meeting and amendment committee are also scheduled in the presence of CReS Kyushu.

### Evaluation of clinical findings and biomarkers

2.5

Clinical objective findings are evaluated by EASI.^[42–44]^ Subjective symptoms are assessed by Patient-Oriented Eczema Measure (POEM)^[44,45]^ and Numerical Rating Scale for Pruritus (Pruritus-NRS) (Fig. 1).^[46,47]^ Patients are also requested to complete Skin Comfort-NRS (0: no discomfort, 10: worst discomfort imaginable) and Treatment Satisfaction-NRS (0: not satisfied at all, 10: very satisfied) (Fig. 1). We measure 18 biomarkers including % eosinophils in blood cell count, LDH, total IgE, soluble interleukin 2 receptor, CCL17, CCL18, CCL22, CCL26, CCL27, IL-13, IL-22, IL-24, IL-25, IL-31, IL-33, TSLP, periostin, and SCCA2. The clinical evaluation and biomarker sampling are performed on the day that injections of dupilumab start and at 2, 4, 8, and 16 weeks (w) of dupilumab treatment (Fig. 2). We also perform proteomic analysis (of roughly 300 proteins) (Myriad RBM, Austin, TX) of the patients’ sera on the day that injections of dupilumab start and at 2w of treatment.

**Figure 1 F1:**
[figure not shown]
Pruritus-NRS, Skin comfort-NRS and Treatment satisfaction-NRS are used in this study. NRS = numerical rating scale.

**Figure 2 F2:**
[figure not shown]
Study calendar is depicted. 1. Subjective clinical evaluation includes POEM, Pruritus-NRS, Uncomfortable skin-NRS, and Treatment satisfaction-NRS. 2. The administration of dupilumab shall be carried out after all assessments and tests are completed. A change of administration day is allowed within the range of +/- 1 week. #3. Use of ocular, intranasal, or inhalant steroids, calcineurin inhibitors, and antihistamines is allowed throughout the study. P = pre-treatment.

### Primary and secondary endpoints

2.6

This is an exploratory clinical study to determine which biomarker is most strongly associated with clinical improvement. The primary endpoint is the association between “baseline levels of 18 biomarkers” and “% change from baseline of EASI at 16w of dupilumab treatment.” Secondary endpoints are

(1)the association between “baseline levels of potential proteomic markers” and “% change from baseline of EASI at 16w,”(2)the association between “baseline levels of 18 biomarkers” and “% change from baseline of POEM at 16w,”(3)the association between “baseline levels of potential proteomic markers” and “% change from baseline of POEM at 16w,”(4)the association between “baseline levels of 18 biomarkers” and “% change from baseline of Pruritus-NRS at 16w,”(5)the association between “baseline levels of potential proteomic markers” and “% change from baseline of Pruritus-NRS at 16w,”(6)the association between “baseline levels of 18 biomarkers” and “% change from baseline of Skin Comfort-NRS at 16w,”(7)the association between “baseline levels of potential proteomic markers” and “% change from baseline of Skin Comfort-NRS at 16w,”(8)the association between “baseline levels of 18 biomarkers” and “% change from baseline of Treatment Satisfaction-NRS at 16w,” and(9)the association between “baseline levels of potential proteomic markers” and “% change from baseline of Treatment Satisfaction-NRS at 16w.”

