### Relationship between biomarkers and clinical findings

3.1

To evaluate the primary and secondary endpoints, we will conduct 2 statistical procedures. First, we will check the distribution of the primary EASI and all secondary clinical findings (POEM, Pruritus-NRS, Skin Comfort-NRS, and Treatment Satisfaction-NRS). The primary EASI and all secondary subjective scores will be logarithmically transformed, and whether the data are normally distributed will be checked. “% change from baseline of EASI and all secondary clinical findings at 16w” will be referred to as the dependent variable, whereas “baseline level of each of the 18 biomarkers” will be referred to as the independent variable.

If we can assume that the data on the log-transformed endpoints at 16w are normally distributed, we will use an analysis of covariance model, adjusting for confounding factors. As potential confounding factors, sex, age, and medical and family history will be included in the model because these are known as important risk factors for AD.

If the data for the log-transformed endpoints at 16w do not fulfil the assumption of normality, we will use generalized linear models, adjusting for confounding factors such as sex, age, and medical and family history.

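### The study aims to determine which of 18 markers is most strongly associated with improvement, but with about 100 patients and one model per marker the top place is unreliable unless one marker clearly dominates

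*Protocol article*

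**What the plan says.** All references are to the protocol article.

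- **Aim.** Section 2.6 opens with "This is an exploratory clinical study to determine which biomarker is most strongly associated with clinical improvement". The primary endpoint is the association of the 18 baseline markers with percentage change in EASI at 16 weeks. The Introduction gives the purpose in the plural, as exploring the markers "that are most strongly associated with clinical improvement in patients with moderate-to-severe AD treated with dupilumab"; the abstract's Discussion is also plural.
- **Candidates.** Section 2.5: "We measure 18 biomarkers including % eosinophils in blood cell count", followed by 17 others. The proteomic panel adds roughly 300 proteins.
- **Analysis.** Section 3.1 takes the baseline level of each marker as the independent variable in an analysis of covariance or generalized linear model, adjusted for sex, age, and medical and family history. Section 3.2 repeats this for each protein. Section 3.3 adds Cronbach's α, factor analysis and combined scores.
- **Size.** Section 2.3: "The target number of 130 patients aimed to be enrolled was determined based on past experiences and feasibility". About a quarter of patients are expected to stop, which is why "a plan was set to enroll more than 130 subjects and perform data analysis of at least 100 subjects". No effect size, power or precision is given.

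**The concern.** Asking which marker is strongest is a question about order. Estimating 18 associations one at a time does not settle it; the estimates still have to be compared. If the leader is chosen and its strength estimated in the same patients, two things follow. The order is uncertain whenever the gaps between markers are no larger than the sampling error. And the leader's estimate is biased upward, because being large is what got it chosen.

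This differs from multiplicity. It happens even when all 18 markers are truly associated with response, so controlling false positives would correct neither the order nor the inflation. The factor scores of section 3.3 do not address it either: they group markers and are related to the endpoints in the same patients.

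At stake is the study's main conclusion. Section 2.1 expects the results to help when the start of a costly drug is being considered, so a leading marker reported without the uncertainty of its lead could be taken as better established than it is.

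**Working it through.** **1. The plan's own figure.** 100 / (1 − 0.25) = 133.3 enrolled; conversely 130 × 0.75 = 97.5 analysed. Both agree with more than 130 enrolled and about 100 analysed. The dropout arithmetic is sound.

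**2. Precision of one association.** For a correlation r, SE ≈ (1 − r²)/√(n − 1). At n = 100:
- r = 0.30: 0.91/9.95 = 0.091
- r = 0.20: 0.96/9.95 = 0.096
- 95% interval (Fisher z) for an observed r of 0.30: 0.11 to 0.47

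For two markers with true r of 0.30 and 0.20, treating their errors as independent, the SE of the difference is √(0.091² + 0.096²) ≈ 0.13. The gap of 0.10 is about 0.75 SE, so a single rival overtakes the better marker in roughly 23% of studies. With several rivals the chance that at least one overtakes it is larger.

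**3. Simulation with all 18 markers.** Multivariate normal data, n = 100, 5,000 studies per setting, markers ranked on absolute sample correlation with the outcome, no covariates. The article gives neither effect sizes nor between-marker correlations. Both are assumed, the latter at 0, 0.3 and 0.5; ranges run over these three values.

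| True correlations (assumed) | True best ranked first | Leader's mean observed r (absolute) | Leader's mean true r |
|---|---|---|---|
| Close rivals: even steps from 0.30 to 0 | 27-34% | 0.35-0.39 | 0.26 |
| Close rivals: even steps from 0.40 to 0 | 35-41% | 0.44-0.47 | 0.36-0.37 |
| Close rivals: best 0.30, other 17 at 0.20 | 25-39% | 0.34-0.38 | 0.23-0.24 |
| Close rivals: best 0.30, five at 0.20, rest 0 | 46-56% | 0.33-0.35 | 0.24 |
| Between: best 0.30, rest 0.10 | 59-81% | 0.31-0.33 | 0.22-0.26 |
| Between: best 0.40, rest 0.20 | 64-86% | 0.41-0.43 | 0.33-0.37 |
| Between: best 0.30, rest 0 | 80-85% | about 0.31 | 0.24-0.26 |
| Dominant: best 0.40, rest 0 | 96-97% | 0.40 | 0.39 |
| Dominant: best 0.50, rest 0.20 | 92-99% | 0.50 | 0.48-0.50 |

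In the four close-rival rows the true best leads in 25-56% of studies, and the leader's |r| is overstated by about 0.07 to 0.16. A repeat run with a different seed gave the same picture, within about two percentage points.

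One caution on the zero-correlation end: with uncorrelated markers, the steps from 0.40 imply a joint R² equal to the sum of the squared correlations, 0.16 × 1785/289 = 0.99, which is not realistic. At correlations of 0.3 and 0.5 the repeat run gives 38% and 42% for that row, so the conclusion does not rest on it.

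**4. A graded case.** Best 0.35, then 0.30, 0.28, 0.25, 0.25, three at 0.20 and the rest 0.15 to 0.05; n = 98, between-marker correlation 0.2 to 0.4. The true best leads in 41-49% of studies. The leader's mean |r| is 0.39-0.40 against a true 0.30-0.31, about 1.3-fold.

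**5. More patients.** With 130 analysed, the steps from 0.30 rise only to 30-37% and the 0.30-against-0.20 case to 31-46%. At between-marker correlation 0.3 and 800 patients they reach 58% and 93%. Enlarging this study is not a practical remedy.

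**6. What a bootstrap of the ranking shows** (n = 100, between-marker correlation 0.3, 300 studies of 200 resamples).
- Steps from 0.30: leader's |r| corrected from 0.36 to 0.28, true value 0.26. Median upper 97.5% rank limit of the leader: 7 of 18.
- 0.30 against 0.20: from 0.36 to 0.27, true value 0.23. Upper limit: 10 of 18.
- One marker at 0.40, rest 0: from 0.39 to 0.34, true value 0.37, so the correction overshoots.

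**The case against.** The best counter-argument is that the article does not commit to a winner. No ranking rule is written, and 18 adjusted associations with their intervals would satisfy the endpoint as defined. Only the sentence in section 2.6 is singular; the abstract, the Introduction and the Discussion speak of biomarkers in the plural. The study calls itself exploratory. Bootstrap and optimism correction are details that an article may leave to an analysis plan that is not shown.

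Much of this stands. A reader might infer that the plan ranks by point estimate; that is the natural route from separate models to a strongest marker, but it is not stated. A reader might also infer that one of about 300 proteins will be named; sections 2.6 and 3.2 promise only associations for proteins. And a reader might infer that a later cohort would fail to reproduce the result; the Discussion says only that comparison with a European cohort will be possible and that the primary endpoints differ. None of these readings is supported.

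It is also fair that the size of the problem rests on assumed effects, that the simulations rank unadjusted correlations whereas section 3.1 adjusts, and that with a dominant marker the problem nearly vanishes.

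What does not fall is the gap between the stated aim and the stated means. This is not a complaint about an omitted detail: section 2.6 sets out to determine which marker is strongest, and separate estimates in about 100 patients may not support that. An exploratory label supports a shortlist better than a single leader.

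**Conclusion.** The point holds in conditional form. The aim in section 2.6 asks more than separate marker models in about 100 patients can reliably deliver, unless one marker clearly dominates. With close rivals the leading marker is the true best in about 25-56% of studies and its |r| is overstated by about 0.07 to 0.16; with a dominant marker it is right in 92-99% with at most about 0.03 overstatement. Intermediate patterns give 59-86%.

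Close rivals are plausible here, because the Discussion describes all 18 candidates as already linked to disease activity and section 3.3 looks for groupings among them. That is a judgement and not a figure in the article. The stronger statement, that the named marker will usually be wrong, is not supported. This is a worthwhile and cheap improvement to the analysis and to the wording of the aim; it does not make the study invalid.

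**What to change.** - In section 3.1, and in 3.2 if proteins are to be ranked, state one common scale on which markers are compared.
- Bootstrap patients (at least 1,000 samples), refitting all adjusted marker models in each, and report a 95% rank interval for every marker.
- Report an optimism-corrected estimate for the leading marker beside the uncorrected one, noting that the correction is approximate and can under- or over-correct.
- Reword section 2.6 so that the conclusion identifies the group of markers whose rank interval includes first place. This agrees with the plural wording in the abstract, the Introduction and the Discussion.

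The cost is a few lines of text and some computing; no new data are needed. The downside is that the headline may be a group of markers with smaller estimates instead of one strong marker.

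### Percent change from baseline is a poor outcome scale for Treatment Satisfaction-NRS: it is undefined at a baseline of 0 and inflated at 1 or 2, which affects secondary endpoints (8) and (9)

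*Protocol article*

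**What the plan says.** Section 2.5 of the protocol article defines the scale as "Treatment Satisfaction-NRS (0: not satisfied at all, 10: very satisfied"), so 0 is a permitted answer at the bad end. It is scored on the day injections start and at later visits. Section 2.6 sets the outcome of secondary endpoints (8) and (9) as the percent "change from baseline of Treatment Satisfaction-NRS at 16w": endpoint (8) for the 18 biomarkers, endpoint (9) for the proteomic markers. Section 3.1 takes the percent "change from baseline of EASI and all secondary clinical findings at 16w" as the dependent variable, and Section 3.2 does the same for the roughly 300 proteins.

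Three further statements bear on the point:

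- Covariates (Section 3.1): "As potential confounding factors, sex, age, and medical and family history will be included in the model". The baseline score of the outcome is not named.
- Transformation (Section 3.1): "The primary EASI and all secondary subjective scores will be logarithmically transformed".
- Entry (Section 2.4): EASI has a floor, "moderate-to-severe patients with EASI score of ≥16, IGA score of ≥3, and body surface area ≥10% at enrollment". Treatment Satisfaction-NRS has none. Patients enter because topical steroids do too little or cannot be advised: "patients in whom topical steroid treatment provides insufficient inhibition or is medically inadvisable".

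**The concern.** Percent change divides by the baseline score. That is harmless when the baseline is well above zero, as EASI is at entry. On Treatment Satisfaction-NRS the worst-off patients sit at or near the zero denominator, and improvement moves away from it. Low satisfaction before dupilumab is plausible in people whose topical treatment has been inadequate, so zeros and ones cannot be dismissed in advance.

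Two things are at stake. Patients with a baseline of 0 drop out of the analysis because of their own answer, and they are the least satisfied. Among those who remain, much of the spread in percent change may reflect the starting score and not satisfaction at week 16. The study looks for the markers most strongly associated with improvement, so a marker that tracks only baseline satisfaction could be ranked as a predictor of response.

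**Working it through.** The article states no expected value, SD or power for this endpoint, so there is no planned figure to reproduce.

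**1. The outcome on its own scale.** From Sections 2.5 and 2.6, with baseline B and week-16 score W, both 0 to 10: percent change = 100 × (W − B)/B. The largest possible rise is 100 × (10 − B)/B; the largest fall is always −100%.

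| B | W = 8 | largest rise |
|---|---|---|
| 0 | undefined | undefined |
| 1 | (8 − 1)/1 = +700% | +900% |
| 2 | (8 − 2)/2 = +300% | +400% |
| 4 | (8 − 4)/4 = +100% | +150% |
| 5 | (8 − 5)/5 = +60% | +100% |
| 8 | 0% | +25% |

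This step needs no assumption. For EASI the denominator is at least 16, so the problem cannot arise.

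**2. Patients without a value.** The baseline distribution is not given, so it is assumed: normal scores rounded and clipped to 0 to 10, SD 2 to 2.5. Patients with a baseline of 0, per 100 analysed:

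| Mean baseline | No value |
|---|---|
| 2 | 23 to 27 |
| 3 | 11 to 16 |
| 4 | 4 to 8 |
| 5 | 1 to 4 |
| 6 | 0 to 1 |

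**3. Share of the variance of percent change explained by the baseline score**, among patients with a baseline above 0:

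- Week-16 mean 8, SD 1.8, correlation with baseline 0 or 0.3, baseline mean 2 to 6, SD 2 to 2.5: 79 to 89%. For absolute change the share is 37 to 67%.
- Week-16 mean 7, SD 2.5, correlation 0.5, baseline SD 2: about 60 to 65% at baseline mean 3 to 4, and about 40% at mean 6.
- The same week-16 assumptions with baseline SD 1.5: 13% at mean 6, where the week-16 score explains 38%. A rerun of this setting at lower means gave 46% at mean 4 and 56% at mean 3.

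The range is therefore 13 to 89%. The share is about 60% or more at a mean baseline of 4 or lower if the baseline SD is 2 or more.

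**4. Effect on a marker.** Assumptions: n = 100 (the minimum analysed number in Section 2.3), baseline mean 3 to 5, SD 2, week-16 score independent of baseline and marker, two-sided 0.05. A marker correlated −0.2 to −0.4 with baseline satisfaction, and unrelated to week-16 satisfaction, is declared associated with percent change in 24 to 83% of simulated studies. With the week-16 score as outcome and baseline as covariate, the rate is 4 to 6%. A marker unrelated to both scores is declared associated with percent change in 5.3% of 4,000 simulated studies, which is nominal.

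**5. The log step.** It does not rescue the outcome. The logarithm of a score of 0, or of a zero or negative percent change, is also undefined.

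**The case against.** The strongest reply is that the size is unknown. The article gives no satisfaction data, and if most patients start near 6 with a narrow spread there are practically no zeros and baseline explains only 13% of the variance. A reader might infer that these endpoints are bound to be driven mainly by baseline and bound to mislead. The documents do not support that; it depends on the distribution. False marker signals likewise need markers that correlate with baseline satisfaction, and nothing in the article shows that any do. For other markers the harm is noise and lost patients. This part of the reply stands.

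A reader might also infer three further things that do not follow:

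- That the baseline rating concerns earlier treatment and the week-16 rating concerns dupilumab, so that the ratio compares two different things. The timing makes this plausible, but the question wording is in a figure that is not shown.
- That the upward direction is itself an error. It only reverses the sign of coefficients. Nor is it an error that patients ending at 8 get different values: absolute change does this too (7, 4 and 0 from baselines of 1, 4 and 8). The fault lies in the zero denominator and the inflation close to it.
- That POEM, Pruritus-NRS and Skin Comfort-NRS need the same change. On Skin Comfort-NRS 0 is the good end ("Skin Comfort-NRS (0: no discomfort, 10: worst discomfort imaginable"), entry requires moderate-to-severe disease, and no calculation here covers those scores.

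It can also be said that a rule for zero baselines belongs in an analysis plan, and that the fallback model in Section 3.1 lists its covariates only as examples. Both are true. But Sections 2.6, 3.1 and 3.2 already fix the outcome scale, and a rule for zeros would not deal with baselines of 1 and 2.

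**Conclusion.** The point holds for secondary endpoints (8) and (9). That the outcome is undefined at a baseline of 0, and can reach +900% from a baseline of 1, follows from the article's own definitions. How much this matters rests on assumed distributions: roughly 0 to 27% of patients without a value, and 13 to 89% of the variance of percent change explained by baseline. The endpoints may mislead; it cannot be said that they will. Two of nine secondary endpoints in an exploratory study are affected, so the point is worth correcting but does not threaten the study's main aim.

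**What to change.** In endpoints (8) and (9) of Section 2.6, and for this score in Sections 3.1 and 3.2, replace percent change by the Treatment Satisfaction-NRS score at week 16, with the baseline score added to the named covariates. State also how the log step applies to this score, since a week-16 score of 0 has no logarithm. The analyses of combined scores in Section 3.3 then follow the same definition.

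The data are already planned for collection, and every patient with both scores is kept. The cost is an amendment to the wording of a registered protocol, and these two endpoints no longer share the percent-change scale of the others, so their coefficients cannot be set directly beside those for EASI or POEM.
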